### Outcomes

#### Primary outcome

The primary outcome of this study will be the perioperative total blood loss (TBL), which is the accumulation of the gross blood losses since operation initiation until postoperative day 3 (POD3). TBL is calculated using the formula provided by Gross [16]:$$ \mathrm{Total}\ \mathrm{blood}\ \mathrm{loss}=\mathrm{PBV}\times \left({\mathrm{Hct}}_{\mathrm{pre}}-{\mathrm{Hct}}_{\mathrm{post}}\right)/{\mathrm{Hct}}_{\mathrm{ave}} $$where PBV refers to the patient’s blood volume, Hct_pre_ is the initial preoperative hematocrit, Hct_post_ is the hematocrit on POD3, and Hct_ave_ is the average of the Hct_pre_ and the Hct_post_.

PBV is then calculated using the formula proposed by Nadler et al. [17]:$$ \mathrm{PBV}={\mathrm{k}}_1\times \mathrm{height}{\left(\mathrm{m}\right)}^3+{\mathrm{k}}_2\times \mathrm{weight}\ \left(\mathrm{kg}\right)+{\mathrm{k}}_3 $$where k_1_ = 0.3669, k_2_ = 0.03219, and k_3_ = 0.6041 for men, and k_1_ = 0.3561, k_2_ = 0.03308, and k_3_ = 0.1833 for women.

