#### Secondary outcomes

Secondary outcomes include:Visible blood losses (intraoperative, postoperative 0–24 h, postoperative 0–48 h, combined perioperative blood loss) and postoperative hidden blood loss (HBL)Postoperative conventional coagulation monitoring indices: PT, APTT, fiber Bragg grating (Fbg), INR, and TEG monitoring indices: reaction time (R time), clot formation time (K time), clot strength (MA), fibrinolysis (LY30)Postoperative hemoglobin nadir (within postoperative 48 h)Perioperative transfusion amounts and ratesPlasma TXA levels tested with solid phase microextraction technique (SPME) [18] 5 min after the last suture (t_4_) and on postoperative day 1 (POD1, t_5_).LOH

Among the preceding indices, combined visible perioperative blood loss refers to the gross visible blood loss since operation initiation until postoperative 48 h. Two pretrained surgeons will take charge of the visible blood loss assessments. Specifically, for intraoperative visible blood loss, it is calculated by weighing surgical sponges, measuring blood collected by suction canisters, and subtracting all irrigations fluids added to the surgical field. For postoperative visible blood losses, since the drainage fluid in the Hemovac includes not only blood but also tissue fluid exudation [19], the actual postoperative blood loss (PBL) will be calculated using our previously reported formula [20]:$$ {\mathrm{PBL}}_{24\mathrm{h}\;\left(48\mathrm{h}\right)}=\mathrm{volume}\ {\mathrm{of}\ \mathrm{drainage}}_{24h\;(48h)}\times {\mathrm{Hct}}_{24\mathrm{h}\left(48\mathrm{h}\right)}/{\mathrm{Hct}}_{\mathrm{ave}} $$where Hct_24h(48h)_ refers to the drainage Hct level tested 24 h or 48 h postoperatively. HBL is also calculated by subtracting the combined visible perioperative blood loss from TBL. All blood losses are determined on the basis of milliliters. If allogeneic transfusion is performed, then TBL is equal to the loss calculated from Hct changes plus the volume transfused.

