### Sample size and statistical analysis

Our pilot cohort study indicated expected TBLs of 971 ± 459 ml and 911 ± 460 ml respectively in the tTXA and ivTXA groups in lumbar spinal decompression and 3–5 levels of bone graft fusion surgeries. Using PASS version 11.0, a sample size of 70 in each group is calculated to be sufficient with assumed type I error rate α = 0.05, power of test 1 – ß = 0.90, and 20% of TBL (195 ml) set as the non-inferiority cut off. Taking into account a dropout rate of 20%, a sample size of 88 in each group is eventually determined.

All the randomized participants who signed the Informed Consent Form (ICF) and satisfied all inclusion/exclusion criteria and have completed demographic data will be included in the intention to treat (ITT) analysis set. All the participants in the ITT set who have completed the perioperative TBL will be included in the per protocol (PP) analysis set. All the randomized participants who have received at least one dose will be included in the safety analysis (SS) set. All the analyses on efficacy will be based on the ITT set. Analysis on AEs will be based on the SS set.

For the primary outcome TBL, statistical methods for continuous variable analysis will be used in the non-inferiority test in the ITT analysis set, and a sensitivity analysis will be conducted in the PP set. The missing data will be treated as missing at random, and the multiple imputation procedure will be used for the primary outcome. The difference between the tTXA group and ivTXA group will be reported as mean difference and lower one-sided 95% confidence interval (CI), along with a one-sided *p* < 0.025.

For other outcomes, the Kolmogorov-Smirnov statistic with a Lilliefors significance level will be used for testing normality for continuous variables. Continuous variables with normal distribution will be compared using the Student *t* test between groups. The continuous parameters with a skewed distribution will be tested with the non-parametric Mann-Whitney *U* test between groups. The categorical variables will be presented as frequencies and percentages and compared using the chi-square test or Fisher’s exact test. If the total number of cases is less than 40 or the minimum expected count is less than 5, Fisher’s exact test will be used.

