There are possible limitations of the TARGETS study. Firstly, there may be concerns that wound irrigation with TXA solution might introduce inconsistent drug delivery doses within the surgical site. However, Ker et al. [34] have found that doses of tTXA administered in RCTs were highly heterogeneous (ranging from 0.7 mg to 100 mg/ml of saline solution), while the hemostatic effect was not dose-dependent. Secondly, as per previous studies, both by our team and others [20, 30], Hct level on POD3 is considered to reach a steady state as the patients are assumed hemodynamically stable, and it is thus adopted for calculating TBL. However, both postoperative transfusions and oral intake may vary with each individual patient, which may exert different effects on the Hct levels. To further establish tTXA as a promising blood conservation strategy in spinal surgeries, larger multicenter investigations are still expected.

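### In transfused patients the primary outcome adds raw transfused volume, not volume weighted by product hematocrit over Hct_ave, so total blood loss is misstated

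*Protocol article*

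**What the plan says.** The Primary outcome section of the protocol article defines TBL as PBV × (Hct_pre − Hct_post)/Hct_ave, where Hct_post "is the hematocrit on POD3". It contains no transfusion term.

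That term appears only at the end of the Secondary outcomes section: after allogeneic transfusion, "TBL is equal to the loss calculated from Hct changes plus the volume transfused". No product type, product hematocrit or conversion is given. The preceding sentences say that "All blood losses are determined on the basis of milliliters" and define hidden blood loss as TBL minus combined visible loss.

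The same section treats drain fluid differently. Because "the drainage fluid in the Hemovac includes not only blood but also tissue fluid exudation", "the actual postoperative blood loss (PBL) will be calculated using our previously reported formula", which multiplies drain volume by drain Hct / Hct_ave.

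The limitations paragraph of the Discussion notes that "both postoperative transfusions and oral intake may vary with each individual patient, which may exert different effects on the Hct levels". It does not mention the added volume or offer a correction.

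**The concern.** The TBL formula does not measure a fluid volume directly. It takes the fall in red-cell volume and restates it as blood at the average hematocrit. Red cells transfused before POD3 raise Hct_post and hide part of that fall, so they have to be added back on the same scale. A millilitre of product counts as one millilitre of patient blood only if its hematocrit equals Hct_ave. The section applies this principle to drain fluid and then drops it for transfused fluid, and it is the unconverted term that enters the primary outcome.

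The comparison at stake is a non-inferiority test with a 195 ml margin. Measurement error that depends on transfusion will move the estimated difference if the arms are transfused unequally, and transfusion need is itself something the treatments may affect. Hidden blood loss carries the same error because it is obtained by subtraction from TBL.

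**Working it through.** **Inputs from the protocol article.** The TBL formula and POD3 hematocrit (Primary outcome); the raw-volume rule and the drain conversion (Secondary outcomes); "expected TBLs of 971 ± 459 ml and 911 ± 460 ml respectively in the tTXA and ivTXA groups" and the 195 ml margin (Sample size and statistical analysis). The expected difference is 971 − 911 = 60 ml. The plan gives no worked example of the transfusion rule, so there is no stated figure to reproduce.

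**Assumptions, not in the documents.** Product Hct 0.50–0.70 for concentrated red cells, about 0.40 for a whole-blood equivalent, 0 for plasma; Hct_ave 0.30–0.40.

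**Step 1, red-cell balance.** With blood volume restored to PBV by POD3 and V ml of product given:

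- red cells lost = PBV × (Hct_pre − Hct_post) + V × Hct_product
- blood lost at Hct_ave = PBV × (Hct_pre − Hct_post)/Hct_ave + V × Hct_product/Hct_ave

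The plan uses V as the last term. The shortfall is therefore V × (Hct_product/Hct_ave − 1).

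**Step 2, shortfall per 200 ml of product.**

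| Product Hct | Hct_ave 0.30 | Hct_ave 0.35 | Hct_ave 0.40 |
|---|---|---|---|
| 0.70 | 267 ml | 200 ml | 150 ml |
| 0.60 | 200 ml | 143 ml | 100 ml |
| 0.50 | 133 ml | 86 ml | 50 ml |
| 0.40 | 67 ml | 29 ml | 0 ml |
| 0 | −200 ml | −200 ml | −200 ml |

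For example, 200 × (0.60/0.35 − 1) = 143 ml. A negative value means that loss is overstated.

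**Step 3, check by simulation.** Stepwise isovolemic loss with PBV 4500 ml, Hct_pre 0.40, true loss 1500 ml, and 400 ml of product given midway:

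| Product Hct | Hct-derived loss | Plan's rule | Hct-weighted rule |
|---|---|---|---|
| 0.70 | 739 ml | 1139 ml | 1497 ml |
| 0.60 | 839 ml | 1239 ml | 1495 ml |
| 0.50 | 942 ml | 1342 ml | 1494 ml |
| 0.40 | 1046 ml | 1446 ml | 1492 ml |
| 0 (plasma) | 1486 ml | 1886 ml | 1486 ml |

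The weighted rule stays within 14 ml of the true loss in every row. The plan's rule does not.

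**Step 4, effect on the group difference.** If mean red-cell volume per patient is D ml higher with tTXA, the tTXA − ivTXA difference is understated by about D × (Hct_product/Hct_ave − 1).

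- D = 50: from 50 × 0.25 = 12.5 ml to 50 × 1.333 = 66.7 ml, or 6% to 34% of 195 ml. At 0.60/0.35 it is 36 ml (18%).
- D = 100: from 25 to 133 ml, or 13% to 68%. At 0.60/0.35 it is 71 ml (36%).
- D = 0: the errors largely cancel.
- D negative: the sign reverses, and the rule works against tTXA.

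**The case against.** The algebra is not in dispute. The objections concern size and direction, and most of them stand.

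- **No document input fixes the size.** Product hematocrit, Hct_ave, transfusion rate, product mix and any imbalance between arms are all absent. If volumes are recorded as whole-blood equivalents, the error is small.
- **Transfusion may be infrequent.** The Participants section excludes pre-existing anemia, unexpected massive bleeding and cell-saver use, and expected mean loss is under one litre. Against that, the Discussion describes transfusion as often needed in this kind of surgery, so it cannot be assumed negligible.
- **Products can offset each other.** At 0.60/0.35, 200 ml of red cells and 143 ml of plasma in one patient net to no error. An article may also leave product definitions to the full protocol, so the plasma and platelet part is only a literal reading that needs clarification.
- **The pilot values may rest on the same rule.** If so, changing the derivation affects how the margin relates to the endpoint.

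A reader might infer that the plan is biased toward declaring non-inferiority. The documents do not support that, because it would require more red-cell use with tTXA and no arm-specific transfusion figure is given. A reader might also set one patient's error, such as 143 ml, against the 195 ml margin. The margin applies to a difference in group means, so that comparison says nothing about the trial's decision.

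None of this makes the stated rule correct. It fixes a weight of 1 for every product, so the problem is more than detail left out of a condensed article.

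**Conclusion.** The concern holds as an error in a stated derivation rule for the primary outcome, and it should be corrected. Under the assumed ranges, TBL is understated by about 50–267 ml for each 200 ml of concentrated red cells and by about 0–67 ml if volumes are whole-blood equivalents. Read literally, the rule overstates loss by the full volume of any plasma or platelets.

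The consequence for the non-inferiority comparison is conditional. An excess of 50 ml of red cells per patient with tTXA would hide about 12–67 ml of the difference, an excess with ivTXA would do the opposite, and equal use would leave little net effect. The documents do not show which case applies.

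**What to change.** Move the rule into the primary outcome definition, before unblinding, and state it as:

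TBL = PBV × (Hct_pre − Hct_post)/Hct_ave + Σ (volume × product Hct / Hct_ave),

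with the sum taken over red-cell products given before the POD3 sample, a prespecified hematocrit for each product type, and no addition for plasma or platelets. Derive hidden blood loss from this TBL. Report the raw-volume version as a sensitivity analysis.

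The cost is mainly in derivation, with no added burden on patients. Two things need checking. The article lists only transfusion amounts and rates as outcomes, so confirm that product type is recorded or take it from transfusion records. If the pilot TBL values were computed with the raw-volume rule, check the basis of the 195 ml margin against the revised definition.

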#### Safety outcomes

The nature, incidence, duration, and severity of AEs, discontinuation due to AEs, AEs occurring during and after intervention discontinuation, body weight, 12-lead electrocardiograms (ECGs), physical examinations, and vital signs will be monitored in this study.

### Data collection and monitoring

Collected data will be entered into electronic case report forms (eCRFs) with double entry and logic validation, and the eCRFs will be uploaded to a central server. To guarantee the quality of trial conduction, a qualified clinical trial expert will be invited to audit the trial implementation process and data entry process every 2 months. The periodic audit is performed to ensure that the protocol and Good Clinical Practices (GCPs) are being followed. The expert may review source documents to confirm that the data recorded on CRFs are accurate. All the study records in the past 2 months will be checked each time to ensure the quality of trial conduct and data consistency between source data and data entered in the database. No interim analysis will be performed in this study.

### Sample size and statistical analysis

Our pilot cohort study indicated expected TBLs of 971 ± 459 ml and 911 ± 460 ml respectively in the tTXA and ivTXA groups in lumbar spinal decompression and 3–5 levels of bone graft fusion surgeries. Using PASS version 11.0, a sample size of 70 in each group is calculated to be sufficient with assumed type I error rate α = 0.05, power of test 1 – ß = 0.90, and 20% of TBL (195 ml) set as the non-inferiority cut off. Taking into account a dropout rate of 20%, a sample size of 88 in each group is eventually determined.

All the randomized participants who signed the Informed Consent Form (ICF) and satisfied all inclusion/exclusion criteria and have completed demographic data will be included in the intention to treat (ITT) analysis set. All the participants in the ITT set who have completed the perioperative TBL will be included in the per protocol (PP) analysis set. All the randomized participants who have received at least one dose will be included in the safety analysis (SS) set. All the analyses on efficacy will be based on the ITT set. Analysis on AEs will be based on the SS set.

For the primary outcome TBL, statistical methods for continuous variable analysis will be used in the non-inferiority test in the ITT analysis set, and a sensitivity analysis will be conducted in the PP set. The missing data will be treated as missing at random, and the multiple imputation procedure will be used for the primary outcome. The difference between the tTXA group and ivTXA group will be reported as mean difference and lower one-sided 95% confidence interval (CI), along with a one-sided *p* < 0.025.

For other outcomes, the Kolmogorov-Smirnov statistic with a Lilliefors significance level will be used for testing normality for continuous variables. Continuous variables with normal distribution will be compared using the Student *t* test between groups. The continuous parameters with a skewed distribution will be tested with the non-parametric Mann-Whitney *U* test between groups. The categorical variables will be presented as frequencies and percentages and compared using the chi-square test or Fisher’s exact test. If the total number of cases is less than 40 or the minimum expected count is less than 5, Fisher’s exact test will be used.

For safety analysis, the AEs and abnormal findings in laboratory tests will be listed with the relationship to the study treatments. Fisher’s exact test will be used to compare the rates of participants who have at least one AE between groups in the SS set.

Statistical analyses will be performed using SPSS version 23.0 software (SPSS Inc., Chicago, IL, USA). A two-sided *p* < 0.05 is considered significant.

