## Methods/design

### Hypotheses

To investigate the non-inferiority of tTXA to ivTXA in blood conservation and clinical safety, our working hypothesis is that tTXA-treated participants suffer *no more* blood losses or allogeneic transfusions, exhibit *undiminished* postoperative hemoglobin level and coagulation function, and are subject to *no increase* in length of hospital stay (LOH) and adverse event (AE) rate compared with those treated with ivTXA.

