## Discussion

It is widely acknowledged that the complexity of multisegmental spinal decompression and bone graft fusion surgery positively correlates with perioperative blood losses. In such surgical arenas, significant blood transfusions are often required, with additional risks of infectious disease transmission, coagulation dysfunctions, and postoperative spinal epidural hematoma formation [21] inevitably introduced. Since ivTXA has been testified as efficacious in reducing blood losses and transfusions in a series of complex surgeries [2, 3, 22], it has also been routinely adopted in spinal surgeries across medical centers.

However, concerns remain over the theoretical thrombogenicity [23] and propensity for convulsive seizures by the use of ivTXA [2, 24]. To settle such concerns, local and more targeted delivery of the drug may provide a promising alternative for blood conservation in spine surgeries while minimizing patients’ systemic exposure to TXA. Currently, the efficacy of tTXA has been well established in major surgeries, especially in hip and knee arthroplasty [12, 14, 25–28]. Yet, clinical research regarding tTXA application in spinal surgeries has been scarce. In a placebo-controlled study, Krohn et al. investigated the impact of tTXA on postoperative blood loss in patients undergoing lumbar instrumented spinal fusion surgery [29]. The wound was irrigated with tTXA for 5 min before removal of excess fluid and wound closure. The postoperative blood loss was reduced by half in patients receiving the treatment, demonstrating the hemostatic efficacy of tTXA. Nevertheless, principal limitations reside in both the quite limited sample size and the placebo-controlled study design; thus, no definite conclusion should be drawn on the comparative hemostatic efficacy of tTXA and ivTXA. Therefore, the present TARGETS study with sufficient sample size will investigate for the first time whether tTXA conveys non-inferior efficacy in managing gross hemorrhage and transfusions compared with ivTXA. With the results of the TARGETS study, we expect to provide high-quality clinical evidence for the role of tTXA in perioperative blood conservation, thereby optimizing the delivery route of TXA in spinal surgeries.

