While visible blood losses are well recognized and researched, the invisible HBL is relatively overlooked, largely due to its residual in dead spaces and extravasation into tissues. However, according to previous studies, both ours and others’, quantities of HBL in spine surgeries are substantial. Smorgick et al. reported that HBL accounted for 39–42% of TBL in primary/revision posterior spinal fusion surgeries [30], and a retrospective study conducted at our center reported the percentage as high as 47% [19, 31]. HBL has been reported as significantly associated with increased postoperative complications and LOH [32]; therefore, it constitutes a crucial component of the enhanced recovery after surgery (ERAS) scheme. Since there has been no study investigating the effect of tTXA on HBL, the issue will be investigated for the first time in this TARGETS study, with the hope that the study results will provide solid evidence for constructing the ERAS scheme in the spinal surgery field.

In the present study, thromboelastography (TEG) will be adopted for real-time evaluation of the coagulation system. By utilizing this dynamic functional hemostatic test, alterations in R time, K time, MA, and LY30 during the coagulation and lytic phases can be identified with minimal delay [33]. Combining the point-of-care (POC) TEG results and the systemic TXA levels revealed by the SPME technique [18], the potential rationale of tTXA on perioperative coagulation function will be precisely depicted, thereby attesting to the hemostatic efficacy as well as the safety profile of tTXA.

The strength of this study is that, for the first time, a prospective, randomized, double-blind, head-to-head study design with sufficient sample size will be adopted to investigate the clinical non-inferiority of tTXA to ivTXA in multisegmental spinal decompression and bone graft fusion surgeries. The results of this study will provide high-quality clinical evidence for the hemostatic efficacy and safety of tTXA application, thereby optimizing the TXA delivery route and the ERAS scheme in spinal surgeries.

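### With the printed planning values, 70 evaluable patients per group give about 41% power at the primary test's one-sided 0.025, not the stated 90%

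*Protocol article*

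**What the plan says.** The section Sample size and statistical analysis takes its planning values from a pilot cohort: "expected TBLs of 971 ± 459 ml and 911 ± 460 ml respectively in the tTXA and ivTXA groups". The margin is "20% of TBL (195 ml) set as the non-inferiority cut off", and the error rate is given as "assumed type I error rate α = 0.05" without saying whether it is one- or two-sided. Power is set at 0.90. From these it concludes that "a sample size of 70 in each group is calculated to be sufficient", raised to 88 per group for 20% dropout.

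The same section judges the primary non-inferiority test at one-sided p < 0.025 and closes with a general two-sided 0.05 threshold. The Hypotheses section fixes the direction of benefit: "tTXA-treated participants suffer *no more* blood losses or allogeneic transfusions". Lower TBL is better, and topical treatment is the test arm.

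The Discussion relies on the result, describing a "head-to-head study design with sufficient sample size will be adopted to investigate the clinical non-inferiority of tTXA to ivTXA".

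**The concern.** In a non-inferiority comparison, power depends on the distance between the assumed true difference and the margin. Here the plan expects the test arm to lose 60 ml more blood, which uses up almost a third of the 195 ml margin (60/195 = 31%). A smaller distance needs more patients, yet 70 per group is fewer than even a zero difference would require at 90% power.

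The primary conclusion is at stake. If power is near 41%, the trial is more likely than not to miss non-inferiority even when the pilot estimates are exactly right. A reader who trusts the printed 90% could then take such a result as evidence against topical treatment. No interim analysis is planned, so no planned look at the data would bring the shortfall to light.

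**Working it through.** **Inputs** (all from Sample size and statistical analysis, except the direction, which is from Hypotheses)
- Means: 971 ml topical, 911 ml intravenous. Difference topical − intravenous = +60 ml, which is worse for topical.
- SDs 459 and 460; common SD = √((459² + 460²)/2) ≈ 459.5 ml.
- Margin M = 195 ml; allocation 1:1; power 0.90; n = 70 evaluable and 88 randomised per group.
- Alpha: one-sided 0.025 for the primary test. One-sided 0.05 is shown as well, because the sidedness of the stated 0.05 is not given.

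**Formulas**
- Distance to the margin: D = M − (assumed true difference).
- Normal approximation: n per group = 2·SD²·(z₁₋α + z₀.₉₀)² / D².
- Power from the noncentral t with 2n − 2 degrees of freedom and noncentrality D / (SD·√(2/n)). With n = 70 the standard error is 459.5 × √(2/70) = 77.7 ml; with n = 88 it is 69.3 ml.

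**Step 1: can 70 be reproduced?** With D = 195 + 60 = 255 ml and one-sided 0.025, the normal approximation gives 2 × 459.5² × (1.960 + 1.282)² / 255² = 68.2, rounded up to 69. The noncentral t gives exactly 70 (power 0.903 at 70, 0.899 at 69). The dropout step is right: 70/0.8 = 87.5, so 88.

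**Step 2: the printed direction.** D = 195 − 60 = 135 ml. At one-sided 0.025 the normal approximation gives 2 × 459.5² × (1.960 + 1.282)² / 135² = 243.5, so 244; the noncentral t gives 245. With n = 70 the noncentrality is 135/77.7 = 1.74 and the power is 40.8%.

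**Step 3: all cases** (noncentral t; one-sided 0.025 / one-sided 0.05)

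| Assumed true difference | D (ml) | n per group for 90% | Power at 70 | Power at 88 |
|---|---|---|---|---|
| +60 ml (as printed) | 135 | 245 / 200 | 40.8% / 53.4% | 49.1% / 61.7% |
| 0 | 195 | 118 / 96 | 70.3% / 80.3% | 79.9% / 87.7% |
| −60 ml (sign reversed) | 255 | 70 / 57 | 90.3% / 94.8% | 95.6% / 97.8% |

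With the difference at +60 ml or at zero, power stays below 90% at both 70 and 88 per group, at either alpha.

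**Step 4: other routes to 70.** Zero difference, one-sided 0.05 and 80% power also give 70 (power 80.3%).

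**The case against.** The best defence is that the article condenses a calculation made in software. The planners may have assumed zero true difference, as is common, with the pilot means printed only as background. One such route does lead to 70: zero difference, one-sided 0.05 and 80% power. But the article prints 0.90, not 0.80, and presents 971 and 911 ml as the expected values. If this is what happened, the stated power is still wrong.

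A second defence is that the dropout allowance provides a reserve. It does not close the gap, since full retention of 88 per group gives 49% (62%).

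Two stronger readings are tempting and should be resisted. A reader might infer that the sign of the difference was certainly reversed in the software. The match at 255 ml makes this the best-fitting explanation at the stated 90% power, but no software input or sign convention is shown, and the 80% route is a rival. A reader might also infer a separate error because 0.05 does not lead to 70. That holds only if 0.05 is one-sided and power is held at 90%. Read as two-sided, 0.05 is the same as the one-sided 0.025 at which 70 does come out, and the section itself uses a two-sided 0.05 elsewhere. What stands is that the cause is unproven. The shortfall does not depend on it.

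**Conclusion.** The stated 90% power does not follow from the printed planning values. For a true difference of +60 ml, SD about 459.5 ml and a 195 ml margin, power with 70 evaluable per group is about 41% at the primary test's one-sided 0.025, or 53% if alpha is one-sided 0.05. With all 88 evaluable it is 49% (62%). Reaching 90% would take about 245 (200) evaluable per group. On the more favourable assumption of zero difference, 70 per group still gives only 70% (80%).

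These figures assume an unadjusted two-sample comparison of means on the ml scale with the pilot SDs. A reversed sign is consistent with the number 70 but is not established by the article. The point must be fixed, because it concerns the primary endpoint and the claims of a sufficient sample size rest on it.

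**What to change.** 1. Check the direction of the expected difference in the sample size calculation against the definition of TBL, where higher is worse.
2. State the assumed true difference and whether alpha is one- or two-sided.
3. Restate the power accordingly: about 41% with 70 evaluable per group at one-sided 0.025 for +60 ml, or 70% if zero difference is the planning assumption, in which case say so.
4. Withdraw the statements, in the abstract and in the Discussion, that the sample size is sufficient.
5. Optionally, prespecify a covariate-adjusted analysis of TBL using baseline variables already collected, such as sex, height, weight, preoperative hematocrit and planned number of levels. The Discussion supports the last in general terms, saying that the complexity of "bone graft fusion surgery positively correlates with perioperative blood losses". The article gives no R², so the gain is an assumption. Multiplying the SD by √(1 − R²), with all 88 per group evaluable and one-sided 0.025, R² of 0.1, 0.2 and 0.3 gives power of 53%, 58% and 64%, against 49% unadjusted. This recovers part of the power and does not restore 90%.

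Steps 1 to 4 need no extra patients; their cost is a less favourable stated power. Step 5 costs one model specification. Recruitment was still open when the article was written. If the sponsor prefers to keep 90% for +60 ml, the price is 245 (200) evaluable per group, or 245/0.8 ≈ 307 (200/0.8 = 250) randomised.
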